**Table 2: Patient outcome measures**

## 2.9 Randomization and allocation concealment

Eligible participants will be randomized in to STOPS group or standard physiotherapy group using web based open source randomization software, by a researcher who is not involved in any other phase of the study (participant screening or enrolment).

To ensure an equal number of participants in both groups and reduce allocation bias, the allocation will be concealed through block randomization. The administrator will create sealed envelopes with allocation information, which will be given to participants by the assessor after the baseline assessment is completed. Both patients and outcome evaluators will be blinded to group allocation.

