# Enrollment

Excluded (n = …) Not meeting inclusion criteria

(n = …)

Refused to participate (n = …)

Other reasons (n = …)

Randomized (n = 150)

Allocated to Usual care intervention

(n = 75)

Received allocated intervention (n = …)

Did not receive allocated intervention (n = …)

(give reasons)

Allocated to Individualised intervention

(n = 75)Received allocated intervention (n = …)

Did not receive allocated intervention (n = …)

(give reasons)

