## 2.8 Baseline evaluation

In addition to demographic and general health information of the participant, all the outcome measures (Table 2) provided below will be evaluated at baseline for both STOPS group as well as standard physiotherapy group. All the baseline assessment will be performed by a Physiotherapist who has a minimum of bachelor level degree and blinded allocation of the groups.

| **Patients’ outcome measures** | |
| --- | --- |
| **Outcome measures** | **Measurement points (**weeks) |
| **Primary outcome measures** | |
| 1. Oswestry Disability Index V2.1 with “sex life” question replaced by a “work/housework” question | 0, 5, 10, 26 and 52 |
| 2.Back pain and leg pain intensity :NPRS | 0, 5, 10, 26 and 52 |
|  |  |
| 3. Resting state functional MRI | 0,26 |
| **Secondary outcome measures** | |
| 1. Brief Pain Inventory | 0, 5, 10, 26 |
| 1. Global rating of change scale (7-point Likert scale) | 5, 10, 26 |
| 1. Satisfaction with treatment (5-point Likert scale) | 5, 10, 26 |
| 1. Interference with work or housework in the past week (5-point Likert scale) and number of hours missed at work in past week. | 0, 5, 10, 26 |
| 1. Örebro Musculoskeletal Pain Screening Questionnaire (ÖMPSQ-SF) | 0, 5, 10, 26 |
| 1. Quality of life (EuroQol-5D-5L) | 0, 5, 10, 26 |
| 1. Depression Anxiety and Stress Scale (DASS-21) | 0, 5, 10, 26 |
| 1. Pain Self-Efficacy questionnaire (PSEQ) | 0, 5, 10, 26 |
| 1. Pain Catastrophizing Scale (PCS) | 0, 5, 10, 26 |
| 1. Insomnia Severity Index (ISI) | 0, 5, 10, 26 |
| 1. Central Sensitisation Inventory (CSI) | 0, 5, 10, 26 |
| 1. Clinical inflammation score | 0, 5, 10, 26 |
| 1. Treatment Credibility Questionnaire | 5, 10, 26 |
| 1. Healthcare utilisation | 5, 10, 26 |
| 1. Compliance with treatment | 5, 10, 26, 52 |
| 1. Resting state functional MRI | 0, 26 |
| 1. Qualitative interviews | At the end of treatment trial 10 |
| 1. Adverse event | 5, 10, 26 |

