## 2.13 Follow-up

Patients will be assessed using self-administered questionnaires that will be filled in physically at the clinic at baseline, at the 5-week and 10-week treatment sessions, and then at the 26- weeks and 52-weeks (for only primary outcomes: disability) post-enrolment.

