## 2.14 Compliance with treatment

A research assistant who is a staff member in department of physiotherapy, JSSCPT and not involved in low back pain treatment will assist participants to complete their questionnaires, which include self-reported measures of compliance with treatment. Day-to-day compliance with exercises will be monitored by the treating physiotherapists as part of their usual practice.

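### Section 2.9 gives participants their allocation and then calls them blinded, so the self-reported outcomes are in effect unblinded and assessor blinding is left unprotected

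*Protocol*

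**What the plan says.** Section 2.1 of the protocol describes the whole study as blinded. Section 2.8 has the baseline assessment "performed by a Physiotherapist who has a minimum of bachelor level degree and blinded allocation of the groups".

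Section 2.9 sets out the allocation process:

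- The sequence comes from randomisation software, run by a researcher with no other part in the study.
- On concealment, it says that "the allocation will be concealed through block randomization". Block size is not given, nor whether it varies.
- An administrator prepares "sealed envelopes with allocation information, which will be given to participants by the assessor after the baseline assessment is completed".
- The next sentence reads "Both patients and outcome evaluators will be blinded to group allocation".

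On data collection, section 2.13 says: "Patients will be assessed using self-administered questionnaires that will be filled in physically at the clinic". Section 2.12 provides a research assistant to help with the questionnaires. Section 2.14 describes this person as departmental staff who is "not involved in low back pain treatment will assist participants to complete their questionnaires".

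**The concern.** Two consecutive sentences of section 2.9 do not fit together. The first puts the allocation in the participant's hands; the second says the participant does not know it.

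This matters more here than in a trial with an independently measured endpoint. The Oswestry (the primary outcome in section 2.12) and the back and leg pain scales (listed as primary in Table 2) are filled in by the patient, so for these measures the patient is the outcome evaluator. If the patient knows the arm, expectation can act directly on the score, and the report would claim a protection that the trial's own procedure removes.

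Two further weaknesses sit in the same section. The assessor, who is meant to be blinded, carries the envelope. And the concealment method named is blocking, which balances the numbers in the arms but hides nothing. If someone involved in recruitment could work out the next allocation, they could influence who is enrolled and when.

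**Working it through.** **Patient blinding.** No figure in the plan bears on this, so the check is a reading of the text.

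1. The envelope holds allocation information and goes to the participant (2.9).
2. No section says that the contents are a neutral code, that the participant leaves the envelope unopened, or that the arms are described to participants in neutral terms.
3. The Oswestry and the pain scales are self-completed (2.12, 2.13).
4. From 1 and 2, the participant knows the arm. From 3, that knowledge reaches the outcome. The sentence on patient blinding therefore cannot stand beside the envelope procedure as written. Resting-state functional MRI, also listed in Table 2, is not self-reported and is not affected by this route.

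**Assessor blinding.** The assessor handles the envelope (2.9) and is called blinded (2.8; outcome evaluators in 2.9). The envelope is sealed and handed over after baseline. The text does not say who opens it, whether it is opened in front of the assessor, or whether the same person sees the patient again at follow-up. The blinding is not shown to fail, but nothing stated protects it.

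**Concealment and predictability.** Blocking conceals nothing. The actual safeguards in 2.9 are the independent sequence generator, the sealed envelopes and release after baseline. Blocking adds a risk only under these conditions:

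- the block size is fixed;
- the observer knows or infers it;
- the observer has learned the earlier allocations in the block.

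The protocol states none of these, so the following is an illustration with assumed block sizes. In a 1:1 permuted block of 2m patients, an allocation is certain once one arm has used its m places. The expected number of such places is 2m/(m+1), so their share of the block is

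[2m/(m+1)] / 2m = 1/(m+1).

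Check for m = 2: the six arrangements are AABB (2 certain places), ABAB (1), ABBA (1) and their mirror images. The total is 2 × (2 + 1 + 1) = 8 of 6 × 4 = 24 places, or 1/3, as the formula gives.

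The flow chart's 150 randomised patients are used for scale. Section 2.5 has 154, but the shares do not depend on the total. The last column is the rate of correct guesses by the same observer, from enumerating all blocks; pure chance gives 50%.

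| Assumed block size | Share certain, 1/(m+1) | Of 150 | Correct guesses |
|---|---|---|---|
| 2 | 50% | 75 | 75% |
| 4 | 33.3% | 50 | 70.8% |
| 6 | 25% | 37.5 | 68.3% |
| 8 | 20% | 30 | 66.6% |
| 10 | 16.7% | 25 | 65.3% |

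If the assessor never learns the contents, or the block size is unknown or varied, no allocation is certain by this route. The range therefore starts at zero.

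**The case against.** The strongest reply is that most of the process is sound. Sequence generation is independent of screening and enrolment, the envelopes are sealed, and they are released only after baseline, so the handover cannot bias the baseline assessment. Carrying a sealed envelope is not the same as knowing its contents. Follow-up help comes from a research assistant who is not said to be the baseline assessor. The clause on blocking can be read as loose drafting. Both arms are active physiotherapy with the same session schedule in Table 3, so keeping patients unaware of which arm is experimental would be feasible.

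Much of this stands, and it rules out two stronger readings.

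- A reader might infer that the assessor learns the allocation and that outcome evaluators are therefore unblinded. The documents do not support that: they do not show the assessor seeing the contents or rating follow-up.
- A reader might infer that later allocations in a block are predictable, for 25 to 75 of 150 patients. The documents do not support that either. The conditions are not stated, recruitment covers an outpatient department and community centres (2.3, 2.4), and nothing says that one person sees every allocation.

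Two things remain. Neutral information for patients may be feasible, but the protocol does not provide for it, so the contradiction on patient blinding is untouched. The assessor risk is also a practical one. Both arms are treated in the same department and its affiliated centres by different therapists (Table 3), so departmental staff could recognise the arm from the therapist. Section 2.14 does not say that the research assistant is blinded.

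**Conclusion.** The concern holds for patient blinding, on the plain text of section 2.9 and without any outside assumption. As written, participants are told their allocation, and the Oswestry and pain scores are in effect unblinded. This should be corrected before enrolment, since a disclosed allocation cannot be hidden again.

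For assessors, the finding is narrower: the blinding stated in 2.8 and 2.9 is left unprotected, not shown to be broken. For concealment, the error is that blocking is named as the method. The size of any predictability is conditional: 50% of patients for fixed blocks of 2, falling to 17% for blocks of 10, for an observer who knows the block size and the earlier allocations, and zero where those conditions do not hold. The protocol does not say which case applies. The size of any resulting bias in the Oswestry cannot be derived from the document.

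**What to change.** 1. **Settle patient blinding in 2.9.** Either state that participants and treating therapists are not blinded and that self-reported outcomes are therefore unblinded, and correct the description in 2.1 to match. Or give participants only a neutral appointment code and describe both arms to them neutrally as physiotherapy programmes.
2. **Take the assessor out of the handover.** Existing staff other than the baseline or outcome assessor should hold and open the envelopes, only after eligibility is confirmed and baseline is complete. Passing the envelope straight to the treating physiotherapist needs care: section 2.10.1 uses the trained physiotherapists' examination to confirm eligibility, so the selection risk could move to them. The order of these steps should be written down.
3. **Describe concealment separately from blocking.** Name the sealed envelopes and the independent sequence generator as the concealment, and use randomly varied block sizes that are not disclosed to recruiting staff.

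The cost is rewording and re-routing among existing staff, with no change in sample size. The downside is that the trial may no longer claim patient blinding.

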## 2.10 Interventions

### 2.10.1 STOPS group

***Classification of patients into subgroups***

Those found to be eligible will be invited to attend individualized assessment with trained physiotherapists. Information from the initial eligibility criteria and physical examination (Appendix 1) will be used to confirm eligibility, determine which subgroup (if any) the patient fits and provide descriptive information on the baseline characteristics of the patients. The patients will be classified into one of the five pre-defined subgroups; i) disc herniation with associated radiculopathy, ii) reducible discogenic pain, iii) non-reducible discogenic pain, iv) zygapophyseal joint dysfunction, v) Sacroiliac dysfunction vi) Non identifiable pathoanatomical disorder, or vii) others subgroup based on information from the eligibility criteria and physical examination. Additionally, patients in all STOPS subgroups will also be further evaluated according to their dominant pain type (nociplastic, neuropathic or nociceptive) using validated assessment. The detailed justification for each of the subgroups has been reported in the previous STOPS classification and treatment protocols.^[14,56-63]^ Additionally, an overview and description of the subgroups is reported in Appendix 2.

**Neuropathic**

**Nociceptive**

**Nociplastic**

**ZJD**

**Other**

**SIJ**

**Inflammation**

**RDP**

**NRDP**

**Radicular disorders**

No identifiable patho-**anatomical** diagnosis

**Depression**

**Anxiety**

**Stress**

**Catastrophizing**

**Pain Self Efficacy**

**Unhelpful motor control strategies**

**Sleep Dysfunction**

**Work issues**

**Unhelpful Beliefs**

**Co morbidities**

**Relationships**

**Readiness for change**

**PTSD**

**Stage 1:**

**Pain type**

**Stage 2:**

**Pathoanatomical diagnosis (if any)**

**Deconditioning**

**Stage 3:**

**Potential barriers to recovery**

**Figure 2: STOPS decision rule algorithm for classifying participants into subgroups**

**STOPS treatment**

Patients will receive individualized physiotherapy sessions, specific to each subgroup, over 10 weeks. The protocols for each subgroup will be outlined in a detailed treatment manual, supplemented by clinical notes which will contain an outline of the treatment protocol including a series of decision-making algorithms on a session-by-session basis. The algorithms (Figure 2) and clinical notes will ensure that essential elements of the treatment program are consistently applied by all physiotherapists across all patients, while still allowing some opportunity for the treatment to be tailored to individual patients. The clinical notes will also require the physiotherapists to document assessment or reassessment findings, clinical reasoning or decision-making rationale, treatment provided and response to treatment during each session. A detailed description (Appendix 2) of the treatment methods, clinical notes and decision-making algorithms for each subgroup will be based broadly on the principles outlined in the Specific Treatment of Problems of the Spine (STOPS) trial treatment protocols. ^[14,56-63]^ A summary of the treatment components is outlined in Table 3.

### 2.10.2 Usual care group

Participants in the usual care receive the routine physical therapy regimen of 10 sessions over 10 weeks

| **Intervention description:** | | | |
| --- | --- | --- | --- |
|  | STOPS physiotherapy | Usual physiotherapy care |  |
| Brief name | STOPS | Usual care |  |
| Why | Improve pain and activity limitation by addressing each participant’s individual barriers to recovery, with better maintenance of treatment effects in the long-term | Short-term relief of pain and function through traditional treatment methods that meet the expectations of participants |  |
| What materials | STOPS treatment protocols.  Decision-making flowcharts.  Treatment based on thorough assessment and questionnaire battery. | Usual care treatment as per protocols followed in Physiotherapy Outpatient Department (OPD) of JSS Hospital, Mysuru, India. |  |
| What procedures | In accordance with published STOPS protocols, modified for persistent pain. | Usual treatment procedures at discretion of physiotherapist |  |
| Who provided | Physiotherapist who has received training in the STOPS approach for managing persistent low back pain | Physiotherapists unfamiliar with the STOPS approach |  |
| How provided | Individual face-to-face sessions | Individual face-to-face sessions |  |
| Where (setting) | Participant with chronic LBP living independently in the community. Treatment provided at Federal Physiotherapy Outpatient Department (OPD) of JSS Hospital, Mysuru, India and the associated community centers affiliated to JSS Hospital. | Participant with chronic LBP living independently in the community. Physiotherapy Outpatient Department (OPD) of JSS Hospital, Mysuru, India and the associated community centers affiliated to JSS Hospital. |  |
| When/how much (dose) | 11 x 45-minute sessions (10sessions in 10 weeks) and the 11^th^ at 6-months post trail commencement | 11 x 45-minute sessions (10 sessions in the 10 weeks) and the 11^th^ at 6-months post trail commencement |  |
| Tailoring | Sessions tailored to the needs and progress of the individual in accordance with the STOPS protocols and detailed assessment profile of the participant | Sessions tailored to the needs and progress of the individual based on standard procedures used by the physiotherapist |  |
| Fidelity checking measures | Physiotherapists must pass a written and practical examination prior to commencing treatment in the trial  A minimum of one treatment session per month will be video recorded and assessed by the researchers for compliance with treatment protocols  Individual patient notes will be reviewed twice throughout the treatment program for each participant by the researchers, to evaluate fidelity and to provide timely feedback | Treatment will be recorded to determine its contents. |  |

**Table 3: Description of experimental and comparison group treatments according to the template for intervention description and replication (TIDieR)**

## 2.11 Treatment fidelity

The Physiotherapists treating the intervention group will undergo a three-month training program in Australia, where they will participate in training and observation sessions with researchers from La Trobe University and Advance Healthcare. These activities will include:

- Observation of Australian physiotherapists trained in the STOPS approach as they assess and manage people with LBP using the STOPS protocols
- Tutorials and peer learning involving Australian physiotherapists and other interns
- Preparation and presentation of case studies
- Intensive study of the STOPS protocols
- Completion of written and practical examinations to ensure sufficient mastery of the protocols to serve the role of the primary clinical contact in India.

After commencing the trial, physiotherapists will be monitored for the quality of their treatment via the following process:

- Regular review of treatment notes by the original STOPS developers ([name] and [name]).
- If the competency and proficiency threshold of “fair” is not met, further top-up training for the physiotherapists will be implemented followed by re-evaluation
- If physiotherapists were not engaged in providing treatment in the trial for longer than 12 weeks, top-up training and re-evaluation will also be implemented.

## 2.12 Outcome measures

A research assistant will be available to assist patients with the questionnaires as needed and to collect them upon completion.

***Primary outcomes***

Activity limitation will be evaluated using nine questions from the Oswestry Disability Index Version 2.1^[66,67]^, with the tenth question relating to “sex life” being replaced by a question relating to “work/housework”.^[67,68]^ The Oswestry is a reliable, valid, and responsive instrument for measuring activity limitation in people with low back pain and referred leg pain.^[69-71]^

***Secondary outcomes***

1. *Back pain and leg pain intensity:* Separate 0-10 Numerical Rating Pain Scales will be administered, one for back pain and another for leg pain. The intensity of pain will be rated on average over the past week, with end-point descriptors of “no pain” and “worst pain possible”.
2. *Pain severity and impact:* Brief Pain Inventory - Short Form (BPI-SF) will be used to assess the severity of pain and the impact of pain on daily functions. The BPI-SF is a 9-item self-administered questionnaire which exists within the [biopsychosocial model](https://www.physio-pedia.com/Biopsychosocial_Model) of pain, as it addresses sensory, emotional, and functional aspects of the pain experience ^[72]^. Thus, the tool is responsive to changes in pain associated with both pharmacological, physical, and psychological interventions^[73]^
3. *Global effect:* Global rating of change will be measured using a 7-point Likert scale, with participants rating their overall change since the baseline assessment as “completely recovered”, “much improved”, “slightly improved”, “no change”, “slightly worsened”, “much worsened”, or “vastly worsened”.^[74-75]^ Various versions of this scale are reliable, responsive, and valid. ^[75-76]^
4. *Satisfaction with treatment:* Participants will rate their satisfaction with physiotherapy treatment on a 5-point Likert scale, with ratings from “very satisfied” to “very dissatisfied”.^[77,78]^This scale has good reliability, validity, and responsiveness. ^[79,80]^
5. *Work interference:* Interference with work due to the LBP will be assessed in two ways. Firstly, at each assessment point, participants will record the number of workdays missed due to their back/leg condition over the previous 30 days. ^[14,56]^ Secondly, participants will rate the degree of interference with work (employment or housework) caused by their back/leg condition over the previous week on a five-point scale ranging from “not at all” to “extremely”. ^[14,56]^ These measurement methods have demonstrated good reliability, validity, and responsiveness ^[81,82]^.
6. *Psychosocial risk factors:* The Short-Form Örebro Musculoskeletal Pain Screening Questionnaire (ÖMPSQ-SF) will be used as a measure of psychosocial risk factors for chronic musculoskeletal pain ^[83,84]^. Although it is more commonly used as a prognostic screening tool at one point in time ^[85]^, in our trial the Orebro will also be administered at each follow-up point to detect changes in psychosocial risk factors over time. This appears justified given that Orebro has good test-retest reliability and internal consistency ^[83,86]^.
7. *Health-related quality of life:* Health-related quality of life will be measured with the EuoQol-5D-5L ^[87]^. Utilities will be calculated according to the validated algorithms of Dolan ^[88]^. The EuroQol-5D-5L has good reliability, validity, and ^responsiveness [89-91]^, and has been used in other low back pain trials ^[64,92]^.
8. *Mental health symptoms:* Mental health symptoms will be assessed using the 21-item Depression Anxiety and Stress Scale (DASS-21). The questionnaire measures the severity of depression, anxiety, and stress from normal to extremely severe ^[93]^. DASS-21 normal score cut-offs are 9 for depression, 7 for anxiety, and 14 for stress and higher scores suggest mild to extremely severe mental health symptoms ^[93]^. DASS-21 shows strong validity, test-retest reliability, internal consistency, and responsiveness ^[93,94]^.
9. *Confidence with activities:* Confidence with activities of daily living despite having pain will be assessed using the Pain Self-Efficacy Questionnaire (PSEQ). The PSEQ is a 10-item scale with a score ranging from 0 to 60, where high scores indicate greater levels of confidence in dealing with pain ^[95]^. The PSEQ has excellent validity, reliability, and responsiveness ^[96]^.
10. *Pain catastrophising:* The 13-item Pain Catastrophizing Scale (PCS) will be used to assess inappropriate coping strategies and catastrophic thinking about LBP. The scale is rated on a 5-point Likert scale ranging from 0 (not at all) to 4 (all the time) ^[97]^. Total scores range from 0 to 52, with higher scores indicating worse catastrophic thinking about LBP ^[97]^. The PCS has been shown to have adequate validity, reliability and responsiveness ^[97,98]^.
11. *Sleep quality:* The Insomnia Severity Index (ISI) will be used to assess sleep quality. The scale comprises 7 questions that assess current sleep problems that are rated on a 5-point Likert scale (‘0’ representing none or not at all and ‘4’ representing very much) ^[99]^. Total scores range from 0 to 28, with higher scores indicating worse insomnia severity ^[99]^. The ISI demonstrated good validity ^[99]^ and responsiveness ^[100]^ and has been used to assess sleep quality in individuals with LBP ^[101]^.
12. *Central sensitisation:* The Central Sensitisation Inventory (CSI) will be used to assess central sensitization symptoms. The CSI is a 25-point scale, rated on a scale of 0 (never) to 4 (always), with a score of more than 40 indicating the presence of central sensitization ^[102]^. The CSI is a useful and valid measure for screening patients with central sensitization symptoms ^[103]^ and has strong psychometric properties ^[104, 105]^
13. *Inflammatory symptoms:* The 4-item clinical inflammation score will be used to assess low back-related inflammatory symptoms. A positive clinical inflammation score of at least 3 of; constant symptoms, morning pain/stiffness greater than 60-min, short walking not easing symptoms and significant night symptoms will be used to inform clinical decision. This scale has been validated and achieved a sensitivity of 90.9%, a specificity of 92.9%, and predictive accuracy of 92.3% ^[106]^.
14. *Treatment acceptability:* The treatment Credibility Questionnaire will be used to determine the acceptability of each treatment approach ^[107]^. Treatment acceptability will be assessed at each follow-up visit via a 4-item questionnaire rated on a scale of 0-10, at this point, how logical does the treatment offered to you seem? At this point, how successful do you think this treatment will be in helping you with your back problem? How confident would you be in recommending this treatment to a friend who experiences similar problems? By the end of your treatment, how much improvement in your back condition do you think will occur? This questionnaire demonstrated high internal consistency and good test-retest reliability ^[107]^ and has been used in LBP trials ^[108, 109]^.
15. *Healthcare utilization:* A patient diary will be used to track healthcare utilization including imaging, medication, and other healthcare services ^[14,56]^.
16. *Compliance with treatment:* The number of treatment sessions attended, and the number of missed or cancelled appointments by each patient will be recorded by the physiotherapists. Patient compliance with the treatment will be reviewed by the physiotherapists at each follow-up visit via direct questioning (on a scale of 0-10, how adherent have you been with following the advice and exercises recommended by your physiotherapist on average over the last month? from “not at all” to “fully”) and by reviewing the patient’s exercise charts ^[14,56]^.
17. Resting state functional MRI data (only for a cohort).Details under (Appendix 4)
18. *Qualitative interviews:* A qualitative study of therapist and patients’ experiences will be nested within the usual care program and quality improvement programme using a semi-structured questionnaire and interviews. Individual interviews lasting for 30-40 minutes will be conducted by a different researcher who has experience in qualitative interviews but was not involved in treating patients in the study. Interviews will be voice recorded, and transcribed verbatim, before undergoing thematic analysis. All discussions will be directed by a flexible topic guide (Appendix 3) developed from the pertinent literature ^[110-113]^. The topic guide comprises semi-structured non-leading questions phrased in clear language.
19. *Adverse events:* Continuous clinical assessment of adverse effects events (harmful or unpleasant) of treatment will be monitored by treating physiotherapists and recorded in their participant clinical notes, per their standard clinical practice. Physiotherapists will routinely enquire with participants each session about their response to treatment and any adverse effects of treatment or prescribed exercises.

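### Adverse events are collected only through each arm's own unblinded physiotherapists and their notes, so counts by arm are open to differential ascertainment of unknown size and direction

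*Protocol*

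**What the plan says.** Item 19 of the secondary outcomes (Protocol, section 2.12) makes the treating therapist both the person who asks and the person who records: events "will be monitored by treating physiotherapists and recorded in their participant clinical notes, per their standard clinical practice". The occasion is the treatment session: "Physiotherapists will routinely enquire with participants each session about their response to treatment and any adverse effects of treatment or prescribed exercises".

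Table 2 (section 2.8) has the row "Adverse event | 5, 10, 26", with no form, question or assessor.

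On blinding, section 2.9 states: "Both patients and outcome evaluators will be blinded to group allocation". Treating therapists are not in that list. Table 3 (section 2.10.2) gives the arms different therapists: STOPS-trained in one, unfamiliar with STOPS in the other.

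The oversight of notes also differs. For STOPS, Table 3 says "Individual patient notes will be reviewed twice throughout the treatment program for each participant by the researchers", to check fidelity and give feedback, and section 2.11 adds regular review of treatment notes by the STOPS developers. For usual care the matching cell says only "Treatment will be recorded to determine its contents".

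A second data route already exists. Section 2.12 says "A research assistant will be available to assist patients with the questionnaires as needed and to collect them upon completion", and section 2.13 has the questionnaires "filled in physically at the clinic at baseline, at the 5-week and 10-week treatment sessions", and again at 26 weeks.

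**The concern.** Adverse events are a listed outcome of a two-arm trial, so counts will be tabulated by arm and read side by side. That reading is safe only if an event has the same chance of being recorded whichever arm it occurs in. Here recording depends on the habits of two separate groups of therapists. Each group knows what it delivers, decides what counts as an effect of treatment, and works under different documentation rules. A difference between arms, or the lack of one, could then partly reflect who wrote things down.

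Enquiry is also tied to attendance. A participant who stops coming, perhaps because treatment hurt, leaves the only route described. Events that were never asked about cannot be recovered at analysis, so this has to be settled in data collection.

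**Working it through.** No figure in the protocol is at stake, so the check compares the relevant places and then illustrates the consequence.

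**1. Conditions for recording an event, by arm**

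| Feature | STOPS | Usual care | Same? |
|---|---|---|---|
| Planned sessions (Table 3) | 11 | 11 | Yes |
| Enquiry rule (item 19) | Each session | Each session | Yes |
| Who asks and records | STOPS-trained therapists | Therapists unfamiliar with STOPS | No |
| Recorder blinded (2.9) | Not listed | Not listed | Yes, neither |
| Required session notes on response to treatment (2.10.1) | Yes | None stated | No |
| Researchers' review of notes (Table 3) | Twice per participant, for fidelity | None stated | No |
| Developers' review of notes (2.11) | Regular, for treatment quality | None stated | No |

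Opportunity to ask is equal by design. Documentation and scrutiny of the notes that hold the adverse-event data are not.

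**2. Whether another route fills the gap**

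- Table 2 gives time points without an instrument.
- The questionnaires printed in the appendix contain no adverse-event item.
- Healthcare use is tracked by diary (item 15) and by mailed questionnaires at 5, 10 and 26 weeks (section 2.15, cost-effectiveness). Neither is described as an adverse-event source.
- Figure 1 has fields for reasons for discontinuation and loss to follow-up in each arm. These can capture a stated reason, but they do not ask about events.

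**3. Illustration (assumed figures)**

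Inputs: 75 per arm (Figure 1). True risk p is equal in both arms. The probability that an event is recorded is s1 in STOPS and s0 in usual care. The values of p, s1 and s0 are assumptions; the protocol gives none.

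Observed risks are p × s1 and p × s0, so the apparent risk ratio is s1 / s0, whatever p is.

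With p = 0.20 and s1 = 0.90, the observed STOPS risk is 0.20 × 0.90 = 18%:

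| s0 | Observed usual-care risk | Apparent risk ratio | Chance of two-sided p < 0.05 |
|---|---|---|---|
| 0.90 | 18% | 1.0 | nominal 5% |
| 0.75 | 15% | 1.2 | about 7% |
| 0.60 | 12% | 1.5 | about 18% |
| 0.45 | 9% | 2.0 | about 36% |

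The last column is the normal approximation for two proportions. For 18% against 12%:

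- pooled standard error = √(2 × 0.15 × 0.85 / 75) = 0.0583
- unpooled standard error = √((0.18 × 0.82 + 0.12 × 0.88) / 75) = 0.0581
- (0.06 − 1.96 × 0.0583) / 0.0581 = −0.93, a probability of about 0.18

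Over true risks of 10% to 40% and the three unequal pairs, that chance runs from about 5% to about 70%. If STOPS therapists under-record instead (s1 = 0.60, s0 = 0.90), the ratio is 0.60 / 0.90 = 0.67. The table shows what a given gap would do. It is not evidence that a gap of any size exists.

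**The case against.** The case on the other side has real content.

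- **Symmetry.** Item 19 sets the same enquiry in both arms, and Table 3 gives both the same 11 sessions. This stands, and it equalises the opportunity to ask. It does not equalise what is written down or attributed.
- **Purpose of the review.** A reader might infer that adverse events are audited in STOPS only. The protocol does not say so: the reviews are for fidelity, feedback and treatment quality, and none is said to extract adverse events. They could raise recording in those notes or leave it unchanged.
- **Participants who stop.** A reader might infer that they are never asked. That goes too far. Table 2 schedules adverse events at fixed weeks, follow-up is timed from enrolment, analysis is by intention to treat, and Figure 1 collects reasons for discontinuation. What stands is that no method is described for asking them.
- **Bias.** A reader might conclude that the harms comparison is biased, or biased against STOPS. The protocol supports neither. Section 2.15 names no between-arm test of adverse events, and the illustrative ratios simply restate the assumed recording rates.
- **Other signals.** The global rating of change extends to the worst category of deterioration, and the diary tracks medication and services. These do not depend on a therapist's view of cause, but the protocol does not designate them as harm data.

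**Conclusion.** The point holds in a limited form. The only adverse-event method the protocol describes relies on unblinded therapists who differ by arm, is restricted to effects they attribute to treatment or exercises, and sits in notes whose documentation and review rules are specified for STOPS only. Counts by arm are open to differential ascertainment. Its size and sign cannot be derived from the protocol; under the assumed recording rates above, the apparent risk ratio ranges from 0.67 to 2.0 with no true difference.

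The conclusion assumes that no follow-up form with an adverse-event item exists beyond what the protocol describes and prints. The primary efficacy analysis is not affected. The change is worth making before enrolment because the missing information cannot be reconstructed afterwards.

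**What to change.** In item 19 and Table 2, name one identical participant-completed item as the source for adverse-event counts by arm. It should ask, without reference to cause, about any new or worsened symptom, emergency visit, hospital admission or surgery since the last assessment. Put it on the existing 5-, 10- and 26-week questionnaires, collected by the research assistant, who under section 2.14 is not involved in low back pain treatment.

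Because section 2.13 has those questionnaires completed at the clinic, state that participants who have stopped attending receive the item with the resource-use questionnaires that section 2.15 already plans to mail at the same weeks. Keep therapist notes in both arms as a supplementary source, reported separately.

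The cost is protocol wording, one questionnaire item and its inclusion in a planned mailing. There are two downsides. More unrelated minor complaints will be recorded. Recall is also longer than with enquiry at every session: about 5 weeks up to week 10, then 26 − 10 = 16 weeks. In that last interval the therapists' own enquiry has only the eleventh session, at six months, so little is lost there.
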